#### Additional analysis

We plan to perform a subgroup analysis on the patients who have had a new ventilation tube inserted after spontaneous extrusion of the first ventilation tube.

#### Analysis population and missing data

We plan to test superiority using the intention-to-treat set, considering all patients as randomized regardless of whether they received the randomized treatment. We propose declaring surgical management superior to sham treatment, only if shown to be superior using the intention to treat analysis set. Further analysis can be done using per-protocol analysis.

## Methods: monitoring

### Data monitoring: formal committee

The study is registered at the local branch of the Danish Data Protection Agency in Region Zealand [18] under the ID “REG-035-2021”. The local branch of the Danish Data Protection Agency is independent of the sponsor-investigator and there are no competing interests.

### Data monitoring: interim analysis

An interim analysis is performed on the primary endpoint when 50% of patients have been randomized and have completed the 3 months of follow-up. The interim analysis is performed by an independent statistician, blinded for treatment allocation.

### Harms

#### Adverse events

An adverse event is any untoward medical occurrence reported by the participant, where no relationship between the adverse event and the device under investigation has been judged by the investigator. An adverse device effect is any untoward and unintended response to a medical device. This includes any event resulting from insufficiencies or inadequacies in the instructions for use or the development of the device. This definition also includes any event that is a result of an error. A serious adverse event is an adverse event that led to:A deathA serious deterioration in the health of a subject that resulted inA life-threatening illness or injuryPermanent impairment of a body structure or a body functionMedical or surgical intervention to prevent permanent impairment to body structure or a body functionRequired in-patient hospitalization or prolongation of existing hospitalizationFoetal distress, foetal death or congenital abnormality, or birth defect

A serious adverse device effect is an adverse device effect that has resulted in any of the consequences characteristic of a serious adverse event or that might have led to any of these consequences if suitable actions had not been taken or intervention had not been made or if circumstances had been less opportune.

Foreseeable adverse device effects are mainly purulent otitis media and persistent perforation after tube extrusion. Adverse events and adverse device effects should be assessed from the day of insertion of the tube until week 12 in the main study and until 3 months after end-points (early termination or 24 months) in the follow-up study.

The following events will be reported:Purulent otitis mediaPersistent perforation > 3 months after tube extrusion

The following events will not be reported:Hospitalization for a procedure that was planned before study participation

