**Outcomes:**

The primary outcome will be the number of spontaneous vertigo attacks lasting more than 20 min and time to treatment failure. In addition to the primary outcome, we will assess various secondary outcomes related to hearing, ear fullness, dizziness, and serious adverse events.

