**Table Tabc:** 

**Secondary outcome**	**Type of data**	**Analysis**
Pure-tone audiometry of affected ear, 4 tone average of 500, 1000, 2000, and 3000 Hz	Continuous	Mixed linear modelling
Pure-tone audiometry of affected ear, 4 tone average of 125, 250, and 500 Hz	Continuous	Mixed linear modelling
The subjective hearing	Continuous	Mixed linear modelling
The subjective intensity of ear fullness/pressure	Continuous	Mixed linear modelling
The subjective intensity of dizziness/unsteadiness	Continuous	Mixed linear modelling
The subjective intensity of tinnitus	Continuous	Mixed linear modelling
Number of subjects leaving	Count	Poisson-regression
Number of subjects satisfied	Count	Poisson-regression
The need for escape medication	Count	Poisson-regression
Serious adverse effects	Binary	Logistic regression
Speech audiometry	Binary data. Dichotomized to > 8% or < 8% decrease in speech audiometry	Logistic regression
AAO-HNS Functional Level Scale	Binary. Dichotomized to a change in > 2 or < 2 levels after 3-months follow-up	Logistic regression, alternatively linear regression with bootstrap

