### Ethics statement

We believe that the potential side-effects of this trial are minimal. Sham surgery will always raise ethical considerations. However, ventilation tube insertion is a swift procedure that is performed in local anaesthesia and can be done within a few minutes. The most frequent complications are infection or persistent perforation in the tympanic membrane. This is unlikely to happen in a healthy membrane and can be fixed with eardrops or a myringoplasty. More importantly, treating thousands of patients with ventilation tubes without any beneficial effects are of even greater ethical concern.

It is essential to provide scientific evidence of whether ventilation tubes work in patients with Menière’s disease or not. A negative finding may save patients from ineffective procedures. A positive finding will help patients with Menière’s disease to better disease control, especially in countries where the use of ventilation tube insertion for Menière’s disease is less prevalent. Furthermore, a positive finding may save patients from ablative treatment or invasive surgery such as endolymphatic sac surgery.

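### The only comparative adverse-event outcome has conflicting definitions and labels, and the one definition written out would drop serious device-related events from the comparison

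*Protocol article*

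**What the plan says.** The safety outcome appears in four places in the protocol article.

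- **Abstract, Outcomes:** the trial will assess "various secondary outcomes related to hearing, ear fullness, dizziness, and serious adverse events".
- **Secondary outcomes (main study 3 months):** serious adverse events are listed, with the definition left to ICH-GCP.
- **Statistics, Outcomes, secondary outcome table:** the row is labelled "Serious adverse effects", treated as binary and analysed by logistic regression.
- **Harms, Adverse events:** an adverse event is an untoward "occurrence reported by the participant, where no relationship between the adverse event and the device under investigation has been judged by the investigator". The next class is separate: "An adverse device effect is any untoward and unintended response to a medical device". Seriousness is then defined once for each class: "A serious adverse event is an adverse event that led to" one of the listed consequences, while "A serious adverse device effect is an adverse device effect that has resulted in any of the consequences characteristic of a serious adverse event", or might have done so in less favourable circumstances.

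The same section requires both classes to be collected: "Adverse events and adverse device effects should be assessed from the day of insertion of the tube until week 12 in the main study". It also names purulent otitis media and persistent perforation as events to be reported.

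**The concern.** A between-group safety comparison should count serious events in both arms by the same rule, whether or not someone attributes them to the treatment. Here the only definition that a clinic can read in the document appears to make attribution part of what counts as an adverse event, and the serious category inherits that condition. Related events go into a parallel category that appears in neither the outcome list nor the analysis table.

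If the data were classified this way, the comparison would be filtered by a judgement that is likely to run differently in the two arms. A serious ear event with a tube in place can readily be attributed to the device. The same event in a sham ear, which holds no device, is more likely to be called unrelated and stay in the count. The filter would then favour the tube in the one adverse-event outcome that the protocol compares.

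**Working it through.** The documents give no rate of serious events, and no stated figure is in question. The check traces the definitions.

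**Step 1. What the Adverse events section implies, read literally.**

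| Class | Condition on relatedness | Condition on who reports | Compared between arms? |
|---|---|---|---|
| Adverse event | no relationship to the device judged | participant | only if serious |
| Serious adverse event | inherited from adverse event | inherited | yes |
| Adverse device effect | response to the device | none stated | no outcome names it |
| Serious adverse device effect | inherited from adverse device effect | none stated | no outcome names it |

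On this reading the two serious classes do not overlap, and only one of them is an outcome.

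**Step 2. What the other sections imply.** The secondary outcome list points outside the document for its definition. The analysis table uses a term that is neither of the two defined serious classes. No section says which governs. One outcome therefore has two competing sources of definition and a third label.

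**Step 3. Effect on the comparison.** For each arm, let U be the number of participants with at least one serious event not judged device-related, and D the number whose only serious events were judged device-related.

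- Counting all serious events: (U + D) in the tube arm against (U + D) in the sham arm.
- Counting by the literal Adverse events wording: U against U.
- Change in the between-arm difference: D(tube) − D(sham).

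Under Interventions, Description, the sham tube is placed on the membrane and taken away in the same procedure. D(sham) should therefore be small, and the change is close to D(tube). Its direction favours the tube. Its size is not known, because the documents give no rate for D.

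**Step 4. The participant-report condition.** Tubes are inspected monthly for the first 3 months. A tube harm found there but not reported by the participant is not an adverse event on the literal wording. It can still be an adverse device effect, because that definition has no reporting condition. An event that the clinic finds, that the participant does not report and that is not a response to the device falls into neither class. For serious events this gap is probably small.

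**The case against.** The strongest reply is that the Adverse events section does not define the outcome. The outcome list does, by reference to ICH-GCP, and nothing says that the Harms wording overrides it. The table's label, if anything, leans towards including device effects. This stands: it cannot be said that the outcome omits device-related harm, only that it would if the written-out definition were used. It does not remove the conflict. An estimated 40 clinics would find one definition in the text and a pointer to another.

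Second, the phrase about judged relationship is ambiguous. It may mean that the event was judged unrelated, that causality has not yet been judged, or that no judgement is needed. On the last reading nothing is excluded. On the second, an event leaves the class once it is judged related. The text does not settle this, and so invites inconsistent classification.

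Third, device effects are assessed and two tube complications are reported, so these harms are not lost from the trial. This also stands. However, neither complication has an outcome or analysis row, and other serious device effects are not named for reporting.

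Three stronger inferences are tempting and are not supported.

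- *A persistent perforation needing surgery shows the loss.* The Ethics statement says that complications "can be fixed with eardrops or a myringoplasty", which suggests this example. But the perforation named for reporting must last more than 3 months after extrusion, and main-study assessment ends at week 12, which is 12 × 7 = 84 days. Even the shortest three calendar months (28 + 31 + 30 = 89 days) exceed that, so the named event cannot fall inside the main-study window under any definition.
- *The trial would publish an empty safety comparison.* This would need an event rate that the documents do not give, and it ignores the separate reporting of device effects.
- *The unblinded specialist decides relatedness.* The judgement is assigned to the investigator. Masking says that the ENT specialist performing the procedure knows the allocation, but no section says that this specialist makes the judgement.

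**Conclusion.** The point holds as a conflict in the text with a conditional consequence. The outcome list, the analysis table and the Adverse events section do not agree on what the only comparative adverse-event outcome is. If the Adverse events wording is applied literally, serious events judged device-related leave the between-group comparison, mostly in the tube arm, although they are still assessed.

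The consequence rests on two assumptions: that sites or analysts classify by the definition written in the protocol rather than by the ICH-GCP reference, and that they read the relatedness phrase as excluding related events. Neither can be confirmed from the document, and the content of ICH-GCP was not relied on. The size cannot be stated. The direction can be: it favours the tube.

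This is not a detail that a condensed article leaves to the full protocol. The article states a definition, and that definition sits badly with its own outcome list. The matter is worth correcting before the outcome is counted, but it does not show that the trial's safety data are unsound.

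**What to change.** - **Harms, Adverse events:** define an adverse event as any untoward medical occurrence in either arm, reported by the participant or found by the clinic, regardless of its relation to the device. Record relatedness as a separate item. The device-effect classes can stay as descriptive subsets.
- **Secondary outcomes and the secondary outcome table:** use one name in both, and state that the outcome counts all serious events in either arm, including serious adverse device effects.

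The cost is wording in three places. Somewhat more events may be counted, mainly in the tube arm. No change to sample size, visits or the analysis model is needed. Events already recorded as serious adverse device effects can be brought into the count, since they are assessed anyway.

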#### Choice of comparator

Open-label trials have shown promising results with about 80–90% of the patients showing significant relief from vertiginous spells during treatment with transmyringeal tubes. In one randomized, single-blinded, controlled trial the long-term effect over 12 months of transmyringeal tubes was compared to that of endolymphatic sac surgery, and no significant differences between the treatments were found [12]. Animal studies have shown that the insertion of a transmyringeal tube prevents the induction of endolymphatic hydrops after ligation of the endolymphatic duct [13]. However, the placebo effect associated with MD treatment is generally considered to be substantial. Therefore, we find it relevant to do a sham-controlled trial. When planning a randomized clinical, placebo-controlled trial, AAO-HNS recommends having a follow-up time of 2 years or more [14].

Every year, a lot of children in Denmark and Sweden are treated with transmyringeal tubes to prevent acute purulent otitis media and to relieve conductive hearing loss due to secretory otitis media. An unknown number of tubes are inserted in adults because of secretory otitis media, tuba aperta, and to treat Menière’s disease. Tube insertion in adults is usually easily performed as an office procedure under topical or local anaesthesia. The main complications from ventilation tubes are purulent otitis media while the tube is in place and persistent perforation after tube extrusion.

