### Interventions

#### Description

The participants will be divided randomly into two intervention arms, an experimental group, and a control group. The procedures are described below.

In both groups, the tympanic membrane will be anaesthetized by local application of topical prilocaine (EMLA) or phenol or by infiltration anaesthesia of the outer ear canal. The choice of method is left to the ear, nose, and throat specialist (ENT specialist).

For the experimental group, insertion of a ventilation tube will be performed. An incision is performed, usually in the lower, anterior quadrant of the tympanic membrane, and the transmyringeal tube is inserted. This procedure is usually painless and well-tolerated.

For the control group, the ENT specialist will touch the tympanic membrane with an alligator ear forceps to simulate getting a paracentesis. In the same procedure, a ventilation tube is placed on the tympanic membrane and removed again afterwards without having made a paracentesis. The reason for the above-mentioned is to simulate getting a paracentesis and insertion of a ventilation tube.

The interventions will be performed after the participant has been included in the trial. To improve adherence to the intervention, the position of the tube will be inspected once every month for the first 3 months. This is to avoid spontaneous extrusion of the tube.

If the tube is spontaneously extruded, a new ventilation tube insertion will be performed. In the same way, if a patient with a sham intervention thinks that the tube has spontaneously extruded, then a new sham procedure will be performed.

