**Timeline:**

t_1_: At one month

t_2_: At two months

t_3_: At three months

t_4_: At three to six months from t_3_

t_5_: At three to six months from t_4_

t_6_: At three to six months from t_5_

t_7_: At three to six months from t_6_

t_8_: At three to six months from t_7_

t_9_: At three to six months from t_8_

^a^Patients will be asked to fulfill a weekly subjective symptom score-scheme regarding dizziness, tinnitus, hearing and aural fullness.

The participants will then be asked if they want to participate in a follow-up study which entails a follow-up every 3 to 6 months for a maximum of 24 months.

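### The main-study window for device effects closes at week 12, so persistent perforation can be recorded only in the optional extension, and only in part there

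*Protocol article*

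**What the plan says.** The Adverse events section of the protocol article sets two assessment windows. In the main study, events and device effects "should be assessed from the day of insertion of the tube until week 12 in the main study". For those who continue, assessment runs "until 3 months after end-points (early termination or 24 months) in the follow-up study".

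The same section says "Foreseeable adverse device effects are mainly purulent otitis media and persistent perforation after tube extrusion". It then lists two events for reporting: purulent otitis media, and a perforation that persists more than 3 months after the tube has been extruded. The list is given once and is not split between main study and extension.

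Four other places bear on this:

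- Choice of comparator: "The main complications from ventilation tubes are purulent otitis media while the tube is in place and persistent perforation after tube extrusion".
- Interventions, Description: "If the tube is spontaneously extruded, a new ventilation tube insertion will be performed". In the sham procedure a tube is laid on the membrane and "removed again afterwards without having made a paracentesis".
- Participant timeline, after the 3-month visits: "The participants will then be asked if they want to participate in a follow-up study".
- Retention: a participant who leaves within the first 3 months is asked to complete a functional level scale. One who drops out later is asked whether trial-relevant data may still be recorded.

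**The concern.** The window and the event definition stand in one section and do not fit together. Main-study assessment is counted from insertion and stops at week 12. The event is counted from extrusion and needs more than 3 months. No course of events after insertion satisfies both.

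The event is one of the two complications that the article itself treats as the main ones, and the more lasting of them. The sham procedure makes no incision, so the harm that cannot be seen belongs in practice to the active arm. An absence of such events at 3 months would carry no information about safety. If participants outside the extension are not checked later, the long-term rate rests on a self-selected part of the tube arm.

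**Working it through.** **Inputs**

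- Main-study window: insertion (day 0) to week 12, so 12 × 7 = 84 days (Adverse events).
- Event: present more than 3 months after extrusion (Adverse events). Let D be the length of 3 months in days. Over calendar start dates from October 2021 to September 2024, D runs from 89 to 92. D = 84 is the reading most generous to the plan, with 3 months taken as 12 weeks.
- Extrusion day x, with x ≥ 0.
- Last main-study visit: 3 months plus or minus 4 days (Participant timeline).
- Extension window: closes 3 months after the end-point E (Adverse events).

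**Main study.** The event is recordable only if a day later than x + D falls on or before day 84, so x ≤ 84 − D − 1.

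| D (days) | Latest extrusion day that qualifies |
|---|---|
| 84 | 84 − 84 − 1 = −1 |
| 89 | 84 − 89 − 1 = −6 |
| 91 | 84 − 91 − 1 = −8 |
| 92 | 84 − 92 − 1 = −9 |

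Every value lies before insertion, so the event cannot be met on any reading.

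**Window stretched to the latest permitted visit.** With the window ending on day D + 4, x ≤ (D + 4) − D − 1 = 3. Only a tube lost by day 3 could qualify, and the Description section has an extruded tube replaced, so that perforation would not be left to be followed.

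**Timing that would be needed.** With D = 91, a tube lost on day 0 needs a check after day 91. A tube still in place at week 12 and lost that day needs one after day 84 + 91 = 175.

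**Extension.** The event is recordable only if x + D < E + D, that is, x < E. A tube out before the end-point can qualify. A tube still in place at the end-point, or lost later, cannot, because more than 3 months cannot then pass before the window closes.

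**Participants outside the extension.** The article states no device-effect check after week 12 for someone who declines, and asks only for a functional level scale from someone who leaves within the first 3 months.

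**Size.** The article gives no perforation, extrusion or uptake rate, so the number of missed events cannot be computed. For scale only: if 30% to 50% declined (an assumption), then 0.30 × 52 = 15.6, about 16, to 0.50 × 52 = 26 of the 52 tube-arm participants would have no stated later check. That counts people without a check, not perforations missed.

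**The case against.** The best defence is that the design is staged. The sentence that stops the main study at week 12 also sets the longer extension window, and the reportable events are listed for the trial as a whole. A late harm may reasonably be left to the long phase. This stands as far as it goes: many perforations among those who continue would be captured. It does not help those who decline, or tubes still in place at the end-point.

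The Retention section also plans contact every third month to the end of the trial and allows for continued data recording after a late dropout. That rules out saying flatly that no one outside the extension can ever contribute. But it does not clearly cover a participant who completes 3 months and declines to continue.

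The article condenses a fuller protocol, which may provide for follow-up of unresolved device effects. So the lack of a later check is weaker evidence than the week-12 limit, which is stated outright and conflicts with a stated definition.

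Two stronger readings are tempting, and the article does not support them:

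- A reader might infer that the serious-adverse-event comparison is truncated as well, since a perforation needing repair could meet the serious-event definition. But serious adverse events are listed as a 3-month outcome, so measuring them over about that period is how the outcome is defined. Nowhere is a perforation said to be classed as serious, and the Ethics statement describes the complications as unlikely in a healthy membrane and treatable.
- A reader might infer that the 3-month report will print a zero and flatter the tube. The article does not say that it will tabulate this event at 3 months, and it names the complication openly in several places.

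**Conclusion.** The point holds as a conflict between two stated rules on harms. Persistent perforation as defined cannot be recorded inside the main-study window. This follows from the article's own wording and needs no assumption about rates. The event is observable only in the optional extension, and there only for tubes out before the end-point. Under the rules as stated, a foreseeable tube-arm harm goes partly unascertained. The direction is clear, but the amount is unknown.

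The conclusion about decliners assumes that the full protocol adds no later check. The primary outcome, the sample size and the efficacy comparison are unaffected. This is a change that should be made, not one on which the trial's main result depends.

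**What to change.** Reconcile the assessment window and the event definition in the Adverse events section, and tie ascertainment of this event to extrusion instead of the visit calendar:

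1. For every tube-arm participant, in the extension or not, obtain eardrum status from the treating clinic's records at a point more than 3 months after the last tube came out, up to one fixed cut-off date common to the trial.
2. Look up sham participants at the same cut-off. They have no extrusion date to trigger a check, and a common date keeps ascertainment comparable between arms.
3. State in the 3-month report that persistent perforation is not estimable at that point.
4. Report the later rate among tube-arm participants whose status is known more than 3 months after extrusion. List separately how many still have the tube in place and how many have missing records. Using the whole tube arm as denominator would count both groups as free of the event and bring the undercount back.
5. Leave the 3-month serious-adverse-event comparison as defined, and report later serious events separately.

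The cost is a few sentences under Harms, one line in the consent form and one record look-up per participant. Some records will be missing, and the final harm table will come later than the 3-month results.

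### The protocol has all adverse events assessed but commits to reporting only two non-serious ones, and only one of these can be compared between arms in the main 3-month study

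*Protocol article*

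**What the plan says.** The subsection on adverse events (Methods: monitoring, Harms) starts from a wide definition: "An adverse event is any untoward medical occurrence reported by the participant". It sets an assessment period: "Adverse events and adverse device effects should be assessed from the day of insertion of the tube until week 12 in the main study", with a longer period for the follow-up study. It names what is expected of the device: "Foreseeable adverse device effects are mainly purulent otitis media and persistent perforation after tube extrusion".

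Two lists follow. The positive one reads "The following events will be reported:Purulent otitis mediaPersistent perforation > 3 months after tube extrusion". The negative one has a single entry: "The following events will not be reported:Hospitalization for a procedure that was planned before study participation".

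Elsewhere, serious adverse events are one of the secondary outcomes compared between groups at 3 months. The table of secondary analyses under Statistics has one harm row, "Serious adverse effects", to be analysed by logistic regression. It has no row for non-serious events, and none for the two listed events.

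The Interventions section exposes both arms to an anaesthetic: "In both groups, the tympanic membrane will be anaesthetized by local application of topical prilocaine (EMLA) or phenol or by infiltration anaesthesia". The experimental arm then has an incision and a tube. The control arm has forceps contact with the eardrum, and a tube laid on it and taken away, without an incision.

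**The concern.** What is assessed and what the text commits to report do not match. Assessment covers every untoward occurrence, while the stated commitment for events below the serious threshold covers two tube complications. The word *mainly* in the sentence on foreseeable effects shows that the protocol itself expects others.

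The harms left between the two lists are those that a sham-controlled trial of a minor procedure should be able to describe: reactions to the anaesthetic, which both arms receive by one of three methods, and injury to the ear canal or eardrum from the incision or from the sham contact. No other outcome in the article captures them.

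The Ethics statement rests the sham design on the belief that side-effects will be minimal. A report confined to purulent otitis media and late perforation could neither support nor refute that belief for the anaesthetic or the sham. With an estimated 40 clinics entering events, an unclear list also invites different practice from site to site.

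**Working it through.** The protocol states no figure on this point, so there is none to reproduce. The check sets the passages side by side, adds one calendar comparison, and ends with an illustration.

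**1. Where each kind of harm has a stated place**

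| Harm | Stated place in the article |
|---|---|
| Serious adverse events | Secondary outcome, compared between groups, logistic regression |
| Purulent otitis media | Positive reporting list |
| Perforation persisting after extrusion | Positive reporting list |
| Vertigo attacks over 20 min | Primary outcome |
| Dizziness, tinnitus, ear fullness, subjective hearing | Weekly scores, each with an analysis row |
| Measured hearing | Two pure-tone averages and speech discrimination, each with an analysis row |
| Pre-planned hospitalisation | Negative list |
| Non-serious anaesthetic reaction | None |
| Non-serious ear-canal or eardrum injury from incision or sham | None |

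**2. Can the two listed events be compared between arms in the main study?**

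*Perforation, sham arm.* The sham as described makes no incision and leaves no tube in place. There is nothing to extrude and no opening to persist, so the event cannot arise from it.

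*Perforation, main-study window.* The window runs from the procedure to week 12: 12 × 7 = 84 days. The definition needs more than 3 months after extrusion: 365 / 4 ≈ 91 days. Even with extrusion on day 0, 84 < 91, so the event cannot be established in the window. Reading week 12 loosely as the 3-month visit hardly helps. That visit has a tolerance of 4 days, so its latest day is about 91 + 4 = 95, and the tube would have to come out within the first 4 days or so. An extruded tube is also to be replaced. In practice the event can be established only in the follow-up study, which participants are asked separately whether to join.

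*Purulent otitis media.* It can occur in either arm and within 84 days.

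Result: of two listed events, one can be compared between arms in the main study.

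**3. Illustration of what may fall between the lists**

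The protocol gives no rates, so the rates here are assumptions. With n = 52 per arm, the probability of at least one event at true frequency p is 1 − (1 − p)^52.

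- p = 5%: 1 − 0.95^52 = 0.93
- p = 2%: 1 − 0.98^52 = 0.65

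A non-serious harm of this frequency would therefore probably be seen at least once in an arm. The calculation shows that such events can be expected to occur. It does not show that they would go unreported.

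**The case against.** Several stronger readings are tempting, and the document does not support them.

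- *Harm reporting is limited to two tube complications.* It is not. Serious adverse events are compared by arm, and the seriousness criteria include permanent impairment of a body structure or function, so major eardrum or hearing injury is covered. Purulent otitis media is not confined to the tube arm.
- *Other non-serious events will be assessed and then withheld.* This is inference. The positive list does not say *only*. The negative list names one item, and would be redundant if the first were exhaustive. An exhaustive first list would also shut out the serious events that the protocol plans to compare. *Reported* is undefined as well, and may mean notification to the sponsor or authorities rather than tabulation in the results.
- *Procedure-related vertigo, tinnitus and hearing loss would be lost.* They would not. An excess in either arm would show in the primary or secondary outcomes, though without attribution to the procedure.
- *The sham arm has no start date for harm assessment.* The visit table places tube or sham at the same inclusion visit, so day 0 is common to both. Only the wording is loose.
- *Perforation makes the comparison unfair.* A harm specific to the active device belongs on the list, and a sham count near zero is a proper comparator.

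It can also be said that a condensed article may leave adverse-event tables to the full protocol or the analysis plan. That is fair, and the mere absence of a table is no finding. But this article does not stay silent: it fixes two explicit lists, and their wording leaves a class of assessed events in neither. The objections narrow the point to a gap in the commitment without removing it.

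**Conclusion.** The point holds in a limited form. Reporting of non-serious harms other than the two listed is not provided for, and the text could be read as excluding them. The harms affected are mainly anaesthetic reactions and ear-canal or eardrum injury from the incision or the sham. In the main study, one of the two listed events can be compared between arms. The other is ruled out in the sham arm by the procedure as described, and in both arms by 84 days against about 91.

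The conclusion rests on taking the lists as written and on the article alone. If the full protocol already commits to tabulating all adverse events by arm, what remains is to align the article's wording and to settle the clash between the window and the perforation definition. The primary comparison is unaffected. The change is worth making because the harm comparison is otherwise incomplete and the remedy is cheap.

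**What to change.** In the adverse events subsection:

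1. State that all adverse events and adverse device effects already being assessed, serious and non-serious, are tabulated by randomised arm, including those attributed to the anaesthetic or to the sham procedure.
2. Keep purulent otitis media and persistent perforation as named events of interest within that table, and keep the exclusion of pre-planned hospitalisation.
3. Say what *reported* means: notification, tabulation in the results, or both.
4. Word the assessment window as starting on the day of the randomised procedure in both arms.
5. Reconcile the week-12 end of the main-study window with the perforation definition, so that it is clear in which part of the study, and in which participants, that event can be counted.

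The events are already to be assessed, so no visit or staff is added. The cost is protocol wording, one extra table and somewhat more event entry for the clinics.
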